### Dissemination of results

The results of the trial will be published in a peer-reviewed journal with open access. To facilitate sharing of the clinical research data, the data from the present study will be made available at the global data sharing enterprise Vivli (https://vivli.org/resources). The Vivli platform provides an independent data repository, search engine, and a secure cloud-based analytics platform.

### Study progress

The trial began recruiting in March 2017. It is expected that recruitment for the study will be completed in 2019.

## Discussion

Previous investigators have shown that tracheal intubation and mechanical ventilation are associated with ventilator-induced lung injury and airway inflammation, which contribute to long-term adverse respiratory consequences [33, 34]. Walsh et al. reported that the duration of tracheal intubation and mechanical ventilation among premature neonates is associated with an increased risk of death or survival with neurocognitive impairment [35]. These observations have led health-care providers to pursue less invasive forms of respiratory support for premature neonates, including nCPAP [9, 10].

nCPAP is an established alternative to intubation and mechanical ventilation for premature infants with respiratory distress [7]. Although meta-analytic data show that early adoption of nCPAP was associated with lower risk of BPD than was observed with intubation and ventilation, a high proportion of neonates are not adequately supported on nCPAP and require tracheal intubation and mechanical ventilation (CPAP failure) [8–10]. In fact, the data suggest that 34 to 83% of premature neonates maintained on nCPAP in the delivery room require tracheal intubation and mechanical ventilation [8–10].

More recently, bubble nCPAP has re-emerged as a potential strategy to address high nCPAP failure rates [13]. Although neonates on bubble nCPAP had lower incidence of respiratory failure (tracheal intubation and mechanical ventilation) than did infants supported on ventilator-derived CPAP, the optimal delivery of nCPAP to premature neonates remains unknown [12, 14, 15]. Recognizing the need for a more efficient bubble nCPAP system among preterm infants [15], investigators designed and developed an alternative device, termed Seattle-PAP [12, 13, 17, 18]. In preclinical studies with juvenile rabbits lavaged to produce pulmonary surfactant deficiency [12, 13, 17, 18], Seattle-PAP provides oscillations in airway pressures at lower frequencies than are observed with other devices [17, 18]. The frequencies of airway pressure oscillations generated by Seattle-PAP are lower than those generated by conventional bubble nCPAP [17, 18]. While conventional bubble CPAP provides stabilization and distension of small airways and alveolar spaces, the range of fluctuations in airway pressure provided by Seattle-PAP may improve recruitment of and ventilation to the low ventilation-perfusion compartments of the lung that contribute to hypoxemia [12].

These observations led to a recent study that compared Seattle-PAP and conventional bubble nCPAP (FP-CPAP) among premature infants with an average GA of 29 weeks. The authors observed, among 40 neonates, reduced breathing effort with Seattle-PAP than with FP-CPAP; however, the study was not designed to detect important clinical differences between the two devices [13]. To recommend Seattle-PAP over the current standard of care (bubble nCPAP), a larger comparative trial is needed. Thus, the present study is designed to compare the incidence of respiratory failure over the first weeks of life between the two groups. While the present study is not designed to determine differences in longer-term clinical outcomes (BPD), prespecified secondary analyses are planned.

We acknowledge a number of challenges in the design of the trial. First, the potential benefits and risks of Seattle-PAP versus conventional bubble nCPAP (FP-CPAP) may not be uniform across infants born at all GAs. To that end, we determined a priori to perform a subgroup analysis on infants born after <27 weeks versus those born after 27 to 30 weeks of gestation. Second, our recruitment window provides enrollment up to 72 h of life, irrespective of previous respiratory support (mechanical ventilation or CPAP) and likely over a wide range of acutely impaired lung function. We recognize that this potential heterogeneity increases the risk of type II errors [36]. Third, some infants allocated to Seattle-PAP may receive a brief period of FP-CPAP prior to randomization, which conceivably could affect the interpretation of the results. We attempted to restrict the impact of this by excluding from the trial infants who have received more than 72 h of FP-CPAP, which we felt to be the shortest window in which seeking parental consent would be feasible. Finally, blinding of the interventions, which would have been preferable from a study design perspective, was not feasible, due to the complexity of building and operating a system that disguised which device was providing respiratory support to the infant, yet allowed the clinical care team to monitor effective engagement of the infant with the pressure-generating system.

The results of the present study will inform the design of larger multicenter trials that investigate more fully the benefits and risks of bubble nCPAP in low- and middle-income countries. Since CPAP failure in developing countries may result in neonatal death, potential use in these countries would be even more attractive [11, 14]. While previous investigators have described barriers to successful use of bubble CPAP in such settings (fixation devices are bulky and cover much of the infant’s face; interference with parental interaction and feeding; trauma to the nasal skin or septum; and need for nursing vigilance to ensure an adequate seal), others have shown that bubble nCPAP can be applied effectively in resource-limited situations [14, 37, 38].

The airway pressure oscillations generated with Seattle-PAP, including the lower frequency of pressure oscillations, are modestly different from those generated with conventional bubble nCPAP [17, 18]. Although preclinical and small clinical studies conducted to date have not indicated there is a greater risk of adverse events associated with Seattle-PAP than with conventional bubble nCPAP [13, 17, 18], the present trial will provide an opportunity to observe any unanticipated SAEs.

Use of CPAP among preterm infants is associated with reduced hospital stay [16] and with savings exceeding $10,000 for every six neonates treated with CPAP [39]. Given the interrelatedness of health, availability of resources, and the constraints on health-care budgets, as well as the substantial resource utilization by preterm neonates, improving health-care status is likely to have important cost implications; thus, we will perform a formal economic evaluation ancillary to the proposed RCT with the goal of informing the practice of effective and efficient health care.

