#### Sample size

Using data from other recent large neonatal randomized trials with similar populations, including the SUPPORT trial and the COIN trial [9, 10], as well as contemporary data within the NCH-NRN, we estimate that the proportion of patients experiencing respiratory failure in the control arm (FP-CPAP) will be 50%. Based on preclinical work, we estimate the failure rate in the Seattle-PAP arm will be 30% [13, 17]. Accounting for two interim analyses, 200 neonates are needed with a two-tailed type I error rate of 0.05 and a power of 80% [25]. Multiples will be randomized as a set to the same study arm, requiring an inflation of the estimate by 1.12 to allow for the design effect due to clustering [26, 27]. Thus, the calculated sample size is 115 infants per treatment arm.

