### Statistical analysis

#### Clinical outcomes

Analyses will be performed using Statistical Analysis Software (SAS) Enterprise Guide version 7.15 (SAS Institute Inc., Cary, NC, USA) using an as randomized (intention-to-treat) principle to compare the primary outcome between treatment arms. Continuous data will be expressed as means with standard deviations or as medians with ranges, whereas categorical variables will be expressed with frequencies and proportions. The primary outcome, and other binary outcomes occurring in at least 5% of patients, will be analyzed using Pearson chi-squared tests. Less common binary outcomes will be compared using Fisher’s exact tests. Risk differences and the number needed to treat, along with their 95% Newcombe hybrid score confidence intervals will be calculated, and risk ratios, and their 95% Koopman asymptotic score confidence intervals, will also be calculated. Normally distributed, continuous outcomes will be compared using Student’s *t*-test, whereas the Wilcoxon rank-sum test will be used to compare continuous outcomes with skewed distributions.

In additional analyses, log binomial regression models will be used to evaluate heterogeneity in the effect of treatment with Seattle-PAP on the primary outcome. Treatment effect heterogeneity will be explored across several clinical characteristics that are known to be associated with CPAP treatment failure: GA, birth weight, and exposure to antenatal corticosteroids [15]. Treatment effect heterogeneity will be tested by evaluating the significance of interactions between the factors of interest and treatment arm in log binomial regression models that include the factor, treatment arm, and their interaction. Effect estimates within subgroups defined by these factors will be expressed as risk ratios with maximum likelihood-based 95% confidence limits. Regression models will be estimated using generalized estimating equations to account for the inherent correlation expected with multiples [27].

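### The article names mixed earlier respiratory support as a type II error risk, but its stated primary test and effect-modifier list use neither prior ventilation nor age at randomisation

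*Protocol article*

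**What the plan says.** Among the design challenges in the Discussion, the second is that infants are enrolled "irrespective of previous respiratory support (mechanical ventilation or CPAP) and likely over a wide range of acutely impaired lung function". The article then states: "We recognize that this potential heterogeneity increases the risk of type II errors". The first challenge (GA) is answered with a planned subgroup analysis. The third (FP-CPAP before randomisation) is answered with a 72 h exposure limit. The second has no stated answer.

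The Clinical outcomes section compares the primary outcome by an unadjusted Pearson chi-squared test. Effect heterogeneity is to be explored over "clinical characteristics that are known to be associated with CPAP treatment failure: GA, birth weight, and exposure to antenatal corticosteroids", each in a model with only the factor, the arm and their interaction.

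Randomization is stratified by GA only. The Sample size section assumes "we estimate that the proportion of patients experiencing respiratory failure in the control arm (FP-CPAP) will be 50"% and "we estimate the failure rate in the Seattle-PAP arm will be 30"%, and continues: "Accounting for two interim analyses, 200 neonates are needed with a two-tailed type I error rate of 0.05 and a power of 80"%. The only allowance on top is for multiples, "requiring an inflation of the estimate by 1.12 to allow for the design effect due to clustering", which leads to "Thus, the calculated sample size is 115 infants per treatment arm".

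**The concern.** The trial pools infants supported on CPAP from birth with infants extubated after up to 72 h of ventilation. Both facts are fixed before allocation. The entry criteria turn on weaning within 72 h, and Data collection takes clinical data from the electronic record, so the variables should be available.

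Three things are at stake.

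- **Precision.** If prior ventilation predicts failure, an unadjusted test forgoes some power.
- **Chance imbalance.** Prior ventilation is not a stratification factor, so the arms can differ on it.
- **Interpretation.** With prior ventilation off the modifier list, the plan does not ask whether the effect is similar in the two kinds of infant.

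Age at randomisation may also bear on the outcome definition. One treatment-failure criterion concerns intubation for surfactant with no extubation by 72 h. If that clock runs from birth, as the 72 h in the Aims does, an infant randomised late has little time at risk for that component on the assigned device.

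The Economic outcomes section adjusts the cost model for baseline prognostic differences. The primary clinical comparison has no such step.

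**Working it through.** **1. Reproduce the plan's sample size.** Inputs from Sample size: 0.50 v 0.30, two-sided 0.05, power 0.80.

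Pooled formula: n = [1.96·√(2·0.4·0.6) + 0.8416·√(0.25 + 0.21)]² / 0.20² = (1.358 + 0.571)² / 0.04 = 93 per arm, 186 in total.

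With continuity correction: (93/4)·[1 + √(1 + 4/(93·0.20))]² = 103 per arm, 206 in total. This is within 3% of the stated 200. Then 206 × 1.12 = 230.7, against the stated 230. The plan's figure is reproduced, and it contains no allowance for mixed prior support.

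**2. Power of the planned test.** Effective size is 230/1.12 = 205.4, about 103 per arm. The normal approximation gives Φ[(0.20·√103 − 1.96·0.693)/0.678] = Φ(0.99) = 0.84. Simulation of the Pearson test gives about 0.85. Interim boundaries of P < 0.001 hardly change this.

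**3. Prior ventilation affects risk only.** The article gives neither the share ventilated nor their risk, so both are assumed. Overall rates are held at 50% v 30%, with treatment as a constant shift on the logit scale. Each scenario has 40,000 simulated trials of 103 per arm, comparing Pearson with a Mantel-Haenszel test stratified on prior ventilation. The Monte Carlo standard error is √(0.85·0.15/40,000) = 0.002.

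| Control-risk gap | Share ventilated | Unadjusted | Stratified |
|---|---|---|---|
| 10 points | 50% | 0.846 | 0.839 |
| 20 points | 50% | 0.845 | 0.849 |
| 30 points | 50% | 0.850 | 0.870 |
| 40 points | 50% | 0.844 | 0.888 |
| 50 points | 50% | 0.845 | 0.916 |
| 10 points | 20% | 0.847 | 0.842 |
| 30 points | 20% | 0.845 | 0.859 |

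The unadjusted test stays near 0.85 throughout. Stratifying changes power by between about −0.7 and +7 points.

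**4. Chance imbalance.** With half ventilated, the between-arm difference in that share has SD √(2·0.25/103) = 0.070, so a 95% range of about ±14 points. At a 40-point gap, an imbalance at that limit moves the raw risk difference by 0.40 × 13.7 = 5.5 points, against a planned 20. The unadjusted test's error rate already allows for such swings. Adjustment removes them from the estimate.

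**5. The effect itself is smaller in ventilated infants.** Control risk is 50% throughout. A share f has a fraction r of the 20-point effect, so the overall difference is 0.20·[(1 − f) + f·r].

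| f | r = 0.5 | r = 0 |
|---|---|---|
| 20% | 0.75 | 0.64 |
| 30% | 0.70 | 0.53 |
| 40% | 0.64 | 0.41 |
| 50% | 0.59 | 0.30 |

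This is the mechanism that takes power below plan, and covariate adjustment does not undo it.

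**6. What an interaction test could show.** Take f = 50%, no effect in ventilated infants and 50% v 30% in the rest, 51.5 per arm in each group. The variance of the difference in log risk ratios is 2/51.5 + (1 + 0.7/0.3)/51.5 = 0.104, so SE = 0.322. Then |ln 0.6|/0.322 = 1.59, and power is Φ(1.59 − 1.96) = 0.36. With f = 30% it is about 0.34.

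**The case against.** The strongest reply is that threat and remedy do not match. If prior ventilation only shifts risk, the planned test keeps its power, above the planned 80%. If it dilutes the effect, adjustment does not help. An unadjusted intention-to-treat comparison is valid, and chance imbalance is not bias. All of this stands, and it limits the point to a modest gain in efficiency and interpretation.

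The size also rests on assumed inputs. The larger gains need control-risk gaps of 30 to 50 points. The simulation ignores GA, so the gain would be smaller to the extent that prior ventilation tracks GA. This stands too.

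A reader might infer that the plan does nothing about the mix. The article does not support that. Ventilation and FP-CPAP before entry are capped at 72 h, randomisation is stratified by GA, and care follows shared guidelines. These bound the mix, though none is offered as the answer to this challenge. A reader might also infer that prior support is the only source of heterogeneity named. It is not: GA comes first and gets a subgroup analysis.

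It may be said that adjusted analyses belong in an unseen analysis plan. That does not dispose of the point, because the article itself states both the primary test and the modifier list.

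**Conclusion.** The point holds in limited form. The article names a source of heterogeneity, says it raises the type II error risk, and then states a primary test and a modifier list that leave it out.

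The size is modest: about 0 to 7 points of power over gaps of 20 to 50 points with half of infants ventilated, and a loss of about half a point at a 10-point gap. These figures assume overall rates of 50% and 30% and 103 effective infants per arm.

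The documents do not support the stronger reading that the trial is underpowered because it does not adjust: unadjusted power is about 85% when those rates hold. If the effect is halved in 20 to 50% of infants, power falls to 0.75 to 0.59 whether or not the analysis adjusts. A subgroup analysis would only describe that, with roughly one chance in three of detecting even a complete absence of effect in ventilated infants.

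**What to change.** Before unblinding, prespecify a covariate-adjusted comparison of the primary outcome that:

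- includes GA stratum, mechanical ventilation before randomisation (yes/no), age at randomisation, birth weight and antenatal steroids;
- accounts for clustering of multiples;
- reports a standardised risk difference and risk ratio beside the unadjusted result.

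State which of the two comparisons is primary, and record that both interim looks (after 25 and 110 infants) took place under the plan without this adjustment. Add prior ventilation to the effect modifiers in the Clinical outcomes section, labelled exploratory and of low power.

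**Cost.** No extra infants, and the variables should be obtainable from the record. A documented, justified amendment is needed because the interim efficacy comparisons are done. If the adjusted analysis becomes primary, the headline p-value comes from a model and not from a two-by-two table. Keeping the unadjusted test primary and the adjusted one as a prespecified companion avoids that, but leaves the power gain outside the primary test.

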### Potential impact

Seattle-PAP is a promising new bubble CPAP delivery system that may reduce the need for tracheal intubation and mechanical ventilation among preterm neonates. The Seattle-PAP trial will provide relevant and timely evidence on the efficacy and safety of the Seattle-PAP device compared to conventional bubble CPAP (FP-CPAP) in this vulnerable subgroup of patients.
